## Abstract

**Background:**

Cognitive control training (CCT) has shown potential to reduce emotional vulnerability in adults and adolescents. However, there is scant literature testing the efficacy of CCT for the reduction of anxiety and transferring the effects to educational outcomes in children. Building on the evidence that a greater ability to suppress a prepotent response (inhibitory control) is associated with higher math achievement in children, it is plausible that training inhibitory processes using a CCT paradigm may be beneficial for reducing anxiety, improving inhibitory control, and in turn increasing math achievement.

**Objective:**

This proof-of-concept study aims to investigate the efficacy of 15 sessions of inhibitory control training for reduction in anxiety and improvement in math achievement in primary school children.

**Methods:**

We will use a 2 (group: CCT, adaptive Go/No-Go vs active control, low-load task) multiplied by 4 (time: pre- vs posttraining vs 1-month vs 3-month follow-up) randomized design in a nonselected sample of 100 children aged 8-10 years. Both groups will complete 10 minutes of daily training for 3 weeks at school. The dependent variables will be anxiety and correlates (Spence Children’s Anxiety Scale, Penn State Worry Questionnaire for Children, Revised Children’s Anxiety and Depression Scale, Child Response Style Questionnaire, and Modified Abbreviated Math Anxiety Scale), inhibitory control (Go/No-Go task), shifting (color-shape shifting task), updating (*n*-back task), and math achievement (Applied Problems, Calculation, and Math Facts Fluency subtests from the Woodcock-Johnson IV Tests of Achievement).

**Results:**

We opened enrollment in September 2023. The initial results are expected to be published in late 2024. We predict that children in the CCT group will show a reduction in emotional symptoms; improvements in inhibition, shifting, and updating performance; and advances in math achievement from pre- to posttraining, and that these effects will be maintained at 1- and 3-month follow-ups, compared to children in the active control group.

**Conclusions:**

The CCT paradigm used in our study will provide a greater understanding of the emotional and cognitive transfer effects on children and inform future work. Specifically, the findings will advance the knowledge of deploying inhibitory control training with children and provide valuable insights into its use for reducing anxiety and advancing math achievement.

**Trial Registration:**

Open Science Framework ofs.io/de2qa; https://doi.org/10.17605/OSF.IO/DE2QA

**International Registered Report Identifier (IRRID):**

PRR1-10.2196/52929

## Introduction

### Overview

Anxiety is the most reported mental health problem in young people across and beyond the pandemic [1,2]. Childhood anxiety is associated with excessive worry, avoidance, physical symptoms, and severe social and academic problems [3]. Interventions for anxiety in children are typically expensive to administer (eg, 1:1 psychological therapy) with long waitlists to see providers in the public health system. Hence, there is a need for novel approaches to closing the treatment gap, that is, reducing the discrepancy between the percentage of children with mental health problems and the percentage who receive treatment [4]. The focus of this proof-of-concept study is treating childhood anxiety by targeting the modifiable cognitive processes that underpin emotional symptoms. We will deliver an intervention at school as part of regular classroom routines and examine its efficacy in reducing anxiety and improving cognitive and academic outcomes (more specifically, math achievement).

Research has shown that the ability to control the focus of one’s attention (attentional control or cognitive control) is vital to learning and requires top-down cognitive processes to coordinate thoughts and behaviors to achieve a goal [5]. Attentional control theory [6] proposes that anxiety upsets the balance between the top-down (goal-driven) and bottom-up (stimulus-driven) attentional processes such that it is associated with increased activation of the stimulus-driven system (ie, attention to internal and external stimuli) and decreased influence of the goal-directed system (ie, attention to task demands). Furthermore, attentional control theory posits that highly anxious individuals direct their attention toward potentially threatening information (eg, worrisome thoughts) which in turn reduces the ability to perform ongoing tasks. The theory suggests that the cognitive processes or executive functions most affected by anxiety are inhibitory control, which requires inhibiting distractors and withholding a dominant response, shifting, which entails switching between tasks or demands of a task, and updating, which requires monitoring and updating information in working memory; see Miyake et al [7]. For example, an anxious child might direct their attention to emotional thoughts and be unable to inhibit distracting worries such as “this work is too hard” or “I might fail” and have difficulty shifting their focus back to the task at hand, and when new information is presented requiring them to update their working memory, the demands of controlling attention are borne out in poorer task performance.

There is growing empirical support for targeting or training the cognitive processes most vulnerable to anxiety (ie, inhibitory control, shifting, and updating) and reducing emotional symptoms in adults [8-12] and adolescents [13]. These paradigms are known by the umbrella term, cognitive control training (CCT) or if directly targeting the inhibitory control function, inhibitory control training. A small number of CCT studies have been conducted with children. Results from a systematic review [14] highlighted that of the 8 studies that showed promise for CCT to reduce anxiety only 2 were conducted with primary school-aged children (younger than 12 years of age). Bigorra et al [15] used commercial working memory training with children of 7-12 years with attention-deficit or hyperactivity disorder (ADHD) and behavioral difficulties and Shanok et al [16] used inhibitory control training with typically developing children aged 8-12 years. Both studies reported reduced anxiety in combination with improved cognitive performance (working memory and inhibitory control, respectively); however, neither study examined the transfer of these effects to educational outcomes.

Research in math achievement in school students supports the importance of cognitive control on executive functioning. For instance, Bull and Lee [17] suggest that during math problem-solving, inhibitory control is needed to suppress unwanted information or inappropriate strategies or prepotent number representations, shifting is required to switch math operations within and between more complex problems, and updating is vital for holding and monitoring information in working memory. However, age-related variances in the development of executive function need consideration, particularly as math skill requirements change across the school years [17]. Updating is associated with math achievement in preschoolers [18] and inhibitory control and shifting have also been implicated in early math skill variability [19]. In primary school children, nonetheless, inhibitory control has been shown to be vital for math achievement [20]. Given that the development of executive functioning increases rapidly in the early years of schooling [19,21] and attenuates in adolescence [22], it is plausible that targeting inhibitory control in children aged 8-10 years may serve to boost math performance at a critical time point. The focus of this study is to use a CCT paradigm to reduce anxiety, improve inhibitory control and in turn, math achievement.

### This Study

This proof-of-concept study will examine the effect of inhibitory control training in typically developing children aged 8-10 years. We will compare emotional symptoms (indexed using self-reported scales of anxiety and correlates), inhibitory control, shifting and updating skills (assessed using computerized tasks), and math achievement (measured using standardized math tests) of children completing 15 sessions of daily inhibitory control training versus an active control task from pre- to posttraining and at 1- and 3-month follow-ups. The study will be conducted in year 4 and 5 classrooms. This study aims to determine whether 10 minutes of daily inhibitory control training for 3 weeks can reduce anxiety (and correlates) and improve math achievement and whether any changes are maintained 1 and 3 months after training.

## Methods

### Ethical Considerations

The University of Queensland Human Research Ethics Committee provided approval to conduct this research (2023/HE000462). Gatekeeper approval was also received from participating education departments and schools. Parent consent and child assent will be gained prior to participation. The trial was registered on the Open Science Framework (ofs.io/de2qa).

### Study Design

We will use a 2 (group: CCT, adaptive Go/No-Go vs active control, low-load task) multiplied by 4 (time: pre- vs posttraining vs 1-month vs 6-month follow-up) randomized design (see Figure 1). Children in both the CCT and active control groups will train for 10 minutes each day for 3 weeks (15 sessions) as part of their daily classroom routine. Changes in the dependent variables (anxiety, worry, depression, rumination, inhibitory control, shifting, updating, and math achievement) will be examined pre- to posttraining, and compared to 1- and 3-month follow-up.

**Figure 1 figure1:**
[figure not shown]
Study flowchart.

### Participants

A nonselect sample of children aged 8-10 years will be recruited from primary schools. An a priori power analysis revealed that 66 participants are required to detect small effects (*d*=0.20) approaching those reported by previous studies with 80% or greater power on primary outcome measures relative to controls [9,23,24]. To allow for approximately 30% attrition we will recruit 100 children proportionately balanced for sex and age across 8, 9, and 10 years. To incentivize enrollment and study completion, participating children will be compensated using monetary tokens redeemed at the end of the study; Aus $ 2.00 (US $1.31) for the completed questionnaires at each of 4 time points and Aus $ 2.00 (US $1.31) for each training session (~Aus $ 40.00; US $26.14 per participant). Given that teachers are required to supervise and monitor the daily training, they will be incentivized for their class’s participation (minimum 20 students) at the rate of 1 teacher relief day for each data collection time point (pre- and posttraining and 1- and 3-month follow-ups).

Primary and P-12 schools, as well as private, independent, and Catholic schools, will be approached regarding participation in the study. A recruitment package of materials (including a university ethics approval letter, gatekeeper permission request, pamphlet, study protocol, participant information sheets for parents, teachers and children, consent forms, and an information sheet about children’s anxiety and depression) will be sent to the school principal to determine interest in participation. Information sessions will be held face-to-face or using a video communications platform (eg, Zoom) for principals, teachers, and parents, as required.

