### Data Analytic Plan

Mixed between-within ANOVA will be used with Group (CCT, aGo/No-Go vs active control; low-load task) as the between-subjects factor and time (pre- vs posttraining vs 1- vs 3-month follow-up) as the within-subjects factor. Separate tests will be conducted with the emotional symptom scores, cognitive measures (ie, accuracy and RT), and math achievement scores as dependent variables. Intention-to-treat analyses will be used to account for missing data, as appropriate. Descriptive and inferential statistics will be performed using SPSS (IBM Corp). We will apply Bonferroni corrections to follow-up tests to control for type 1 error.

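### The study is framed as treating childhood anxiety, but the stated whole-group analysis of an unselected sample cannot alone show whether anxious children benefit, and the conclusion is not limited accordingly

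*Protocol article*

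**What the plan says.** The Introduction (Overview) sets a treatment aim: "The focus of this proof-of-concept study is treating childhood anxiety by targeting the modifiable cognitive processes that underpin emotional symptoms". The same section speaks of closing a treatment gap, and for mechanism it draws on a theory about anxious people: "attentional control theory posits that highly anxious individuals direct their attention toward potentially threatening information".

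The population is defined more broadly. The Abstract's objective concerns "reduction in anxiety and improvement in math achievement in primary school children", and This Study says it will "examine the effect of inhibitory control training in typically developing children aged 8-10 years". Under Participants, "A nonselect sample of children aged 8-10 years will be recruited from primary schools". Recruitment is to be balanced for sex and age; anxiety level is not mentioned.

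The Data Analytic Plan reads "Mixed between-within ANOVA will be used with Group (CCT, aGo/No-Go vs active control; low-load task) as the between-subjects factor", with "time (pre- vs posttraining vs 1- vs 3-month follow-up) as the within-subjects factor". It adds that "Separate tests will be conducted with the emotional symptom scores, cognitive measures (ie, accuracy and RT), and math achievement scores as dependent variables". No baseline-anxiety covariate or moderator is stated.

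The Discussion says the results will indicate whether the training is promising as an anxiety intervention for this age group. Its limitations cover the small sample, the narrow age range and untested educational outcomes, but not the anxiety level of the children enrolled.

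**The concern.** The framing and the estimate concern different groups. Treating anxiety and closing a treatment gap are about children who have an anxiety problem. The stated analysis averages over all enrolled children, whatever their anxiety before training.

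Two inferences are at risk. A null whole-group result could be taken to mean that the training has no promise for anxious children, although their effect was not estimated separately. A small positive mean could be taken as evidence of treatment benefit, although it would not show whether the children with elevated anxiety contributed to it. The Spence Children's Anxiety Scale is completed by every child before training, so the information to examine this is already collected.

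**Working it through.** **1. The plan's own figures.** Participants gives d = 0.20, 66 children required and 100 recruited for about 30% attrition. The attrition step is consistent: 66 / 0.70 = 94.3, so 95 are needed and 100 suffices; 100 × 0.70 = 70 remain. The 66 itself does not follow from the stated inputs. A plain two-group comparison at d = 0.20 needs 786 in total (80% power, two-sided 0.05 assumed), and a 2 × 4 interaction test with f = 0.10 reaches 66 only at a repeated-measures correlation near 0.76, which is not stated. That is a separate matter and is not evidence for this point. Here 0.20 serves only as the planned effect, and 70-100 as the likely analysed number.

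**2. What the documents do not give.** There is no baseline mean, SD or share of children with elevated anxiety. Everything below is therefore conditional on assumed values.

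**3. Dilution.** Let p be the share of children with elevated anxiety and d_sub the effect in them, and assume no effect in the rest. Then whole-group d = p × d_sub.

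| p | d_sub = 0.5 | d_sub = 0.8 | d_sub needed for whole-group 0.20 (0.20 / p) |
|---|---|---|---|
| 0.1 | 0.05 | 0.08 | 2.0 |
| 0.2 | 0.10 | 0.16 | 1.0 |
| 0.3 | 0.15 | 0.24 | 0.67 |
| 0.5 | 0.25 | 0.40 | 0.40 |

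The range includes values above the planned 0.20. If the effect is the same in all children, there is no dilution at all.

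**4. Power in one assumed scenario.** Assume p = 0.19, d_sub = 0.5 and a baseline-to-outcome correlation r = 0.7. The whole-group effect is 0.19 × 0.5 = 0.095 SD. For a baseline-adjusted comparison of two equal groups, SE = √(1 − r²) × √(4/N), with √(1 − 0.49) = 0.714.

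- N = 70: SE = 0.714 × 0.239 = 0.171; 0.095 / 0.171 = 0.56; two-sided power about 9%.
- N = 100: SE = 0.714 × 0.200 = 0.143; 0.095 / 0.143 = 0.67; power about 10%.

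Simulation with a skewed baseline agrees: about 8% and 9-10%. These figures reflect the small sample as well as dilution. A uniform effect of 0.20 SD would itself be detected in only about 22% (N = 70) and 29% (N = 100) of simulated trials.

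**5. What a Group-by-baseline term would deliver.** In the same simulated scenario, the interaction is significant in about 14% of trials at N = 70 and 19% at N = 100. The fitted group difference at the 80th percentile of baseline averages about 0.21 SD, although the true effect in the elevated children is 0.5, because a straight line spreads a confined effect over the whole range. Its SE is about 0.22 (N = 70) or 0.18 (N = 100), so the 95% CI is about ±0.43 or ±0.35. Under a uniform 0.20 SD effect the same fitted value also averages about 0.20. That single number therefore cannot tell the two situations apart.

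**6. Gain from baseline adjustment.** For change scores, SE = √(2(1 − r)) × √(4/N). At r = 0.7 and N = 70 this is 0.775 × 0.239 = 0.185, against 0.171 with adjustment. The gain is modest, but the score is already available.

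**The case against.** The unselected sample is a declared choice that fits the objective and the aim. For that population the group mean is the right quantity, and the Discussion asks about promise in the age group, not in anxious children specifically. The Introduction also cites an inhibitory control training study in typically developing children that reported reduced anxiety, which counts against assuming no effect in less anxious children. The study is labelled proof-of-concept, and its Discussion already warns about generalising. A moderator analysis may be in a fuller plan that is not shown.

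Most of this stands. Recruitment is not an error, and the absence of a moderator from a condensed article is not by itself a fault. What remains is visible in the article: a treatment framing and a planned interpretation that are not tied to the population studied, with limitations silent on anxiety level. The cited study, as described, does not say which children improved.

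A reader might infer more: that most children in the classes have too few symptoms to improve, so the trial is bound to miss a real benefit. The documents do not support that. The Spence total sums 38 items scored 0-3, a range of 0-114, and a scale that starts at zero does not establish a floor problem without a baseline distribution. Nor does any section say that a null would be read as no promise for anxious children; the wording merely leaves that reading open.

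A reader might also infer that an interaction test would settle who benefits. Its low power, and the understatement by a linear term, show that it would not.

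**Conclusion.** The point holds as a mismatch between framing and estimate. The stated analysis answers a question about unselected 8-10-year-olds; the Introduction and Discussion invite a conclusion about treating anxiety. The size of any dilution cannot be established. The range of 0.05-0.15 SD rests on three assumptions: that 10-30% of children are elevated, that they gain 0.5 SD, and that the others gain nothing. The power figures further assume r = 0.7, a skewed baseline and two equal groups. The consequence is for interpretation: the planned test remains valid for its own population, and nothing here calls for selective recruitment.

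**What to change.** - **Recruitment:** keep it as it is.
- **Wording:** in the Introduction and Discussion, limit the conclusion, whether positive or null, to unselected children aged 8-10 years. Add to the limitations that the whole-group mean does not show the effect in children with elevated anxiety.
- **Analysis of the Spence total:** compare posttraining and follow-up scores between groups, adjusted for the continuous pretraining total.
- **Exploratory term:** prespecify one Group-by-pretraining-Spence term for that outcome. Report it as an estimate with 95% CI, labelled exploratory, and not as a test of benefit in anxious children. Fix it before analysis, so that a high-anxiety subgroup is not chosen after a null result.
- **Optional:** balance allocation on the pretraining Spence total, if randomisation can follow the pretraining questionnaire.

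The cost is a few sentences, one covariate and one secondary estimate from data already collected. The downside is that the interaction is imprecise at 70-100 children and, being linear, understates an effect confined to a high-anxiety minority. The plan should therefore state that a null interaction is not evidence of no benefit in anxious children.

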#### Training Groups

We will randomly assign participants to 1 of the 2 training groups. Groups comprise an experimental CCT group that will train using an adaptive Go/No-Go Task (aGo/No-Go) targeting inhibitory control, and an active control group that will train using a low-load task. The active control task does not require the same cognitive load as the aGO/No-Go task; thus, we do not expect it to produce emotional or cognitive changes. Children in both groups will undertake 10 minutes of training per day for 3 weeks, allowing 15 sessions to be completed.

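### The stated 66 participants do not give 80% power for a between-group difference of d=0.20 under any usual within-child correlation; the detectable effect should be restated

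*Protocol article*

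**What the plan says.** The sample size is justified in one sentence of the Participants section: "66 participants are required to detect small effects (*d*=0.20) approaching those reported by previous studies with 80% or greater power". The sentence goes on to say that this power applies "on primary outcome measures relative to controls", so the effect is a difference between the two arms. The next sentence sets recruitment: "To allow for approximately 30% attrition we will recruit 100 children".

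The design has two arms. The Training Groups section says "We will randomly assign participants to 1 of the 2 training groups". The Data Analytic Plan says "Mixed between-within ANOVA will be used with Group" as the between-subjects factor and four assessment times as the within-subjects factor. The article does not give the test, alpha, sidedness or within-child correlation behind the figure of 66.

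**The concern.** A standardised difference of 0.20 between two independent groups usually takes several hundred children to detect, so 66 looks far too few. Repeated assessments can reduce the number, but only to the extent that a child's scores are strongly correlated over time. The question is whether any reasonable correlation makes the sentence true.

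This is the only quantitative justification of the sample size in the article. If the figure is wrong, the study is described as able to detect small effects when its reach is really moderate effects or, with very stable measures, effects of about 0.3 SD.

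**Working it through.** **Inputs from the article:** d=0.20 relative to controls; 66 participants; power of at least 80%; two groups; four assessments; about 30% attrition; 100 recruited.

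**Assumed, because not stated:** two-sided alpha 0.05; 1:1 allocation (the most favourable ratio); SD 1 and an equal correlation r between any two assessments; no group difference at baseline and the same difference d at the three later times. The range of r is shown.

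**Attrition step.** 66/0.7 = 94.3, rounded up to 95, and 100 × 0.7 = 70. Recruiting 100 is consistent with needing 66, so this step is sound.

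**1. Single between-group comparison.** The noncentrality is d × √(N/4) = 0.20 × √16.5 = 0.81 on 64 degrees of freedom, which gives power of 12.6%. It is 13.1% with 70 children and 16.8% with all 100. The normal approximation for 80% power gives 2 × (1.96 + 0.8416)² / 0.04 = 392.4, or 393 per arm (786 in total). The exact t calculation gives 394 per arm (788).

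**2. Planned 2 × 4 group-by-time test.** The group differences over time are (0, d, d, d). Their mean is 0.75d, and the sum of squared deviations is (0.75d)² + 3 × (0.25d)² = 0.75d². Therefore

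λ = (N/4) × 0.75 × d² / (1 − r), with 3 and 3(N − 2) degrees of freedom.

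For N=66 and d=0.20, λ = 16.5 × 0.75 × 0.04 / (1 − r) = 0.495 / (1 − r).

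| r | λ at N=66 | Power, N=66 | Power, N=100 | d detectable at 80%, N=66 to 70 |
|---|---|---|---|---|
| 0.5 | 0.99 | 11.4% | 15.1% | 0.67 to 0.65 |
| 0.7 | 1.65 | 16.2% | 23.0% | 0.52 to 0.50 |
| 0.8 | 2.475 | 22.7% | 33.3% | 0.42 to 0.41 |
| 0.9 | 4.95 | 42.8% | 61.6% | 0.30 to 0.29 |

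At r=0.95, λ is 9.9 and power is 74.7%. At r=0.96, λ is 12.375 and power is 84.4%. So 66 children reach 80% only between these two values. The total N needed for 80% power is 730, 438 and 294 at r=0.5, 0.7 and 0.8, and 148 at r=0.9. For the single comparison, the detectable d with 66 to 70 children is 0.70 to 0.68.

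**3. Other analyses, N=66, d=0.20.**

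| Analysis | r=0.5 | r=0.8 | r=0.9 |
|---|---|---|---|
| Pre-post change score | 12.6% | 24.4% | 43.2% |
| Post-training score adjusted for baseline | 15.2% | 26.6% | 45.1% |
| Baseline versus mean of three later times | 16.5% | 34.1% | 59.2% |
| Mean of three later times adjusted for baseline | 23.6% | 39.0% | 62.5% |

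The two averaged analyses pass 80% only at r of about 0.94. A one-sided single comparison has 20.0% power.

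**4. Can 66 be reproduced?** Yes, with a different effect size. If the interaction effect is entered directly as f=0.10, the usual formula is λ = f² × N × 4 / (1 − r). At r=0.77 this gives 0.01 × 66 × 4 / 0.23 = 11.48 and power of 81.3%, and 66 is the smallest even N that reaches 80%. Equating this λ with that in step 2 gives d² = 0.01 × 4 × 4 / 0.75 = 0.213, so d = 0.46. An interaction f of 0.10 is therefore a sustained group difference of about 0.46 SD here, not 0.20.

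**The case against.** The best defence is that the article condenses a fuller protocol. The test and correlation may be given there, and the near-exact match at f=0.10 suggests that a real calculation was run. Part of this stands: leaving those inputs out of an article is no fault, and the origin of 66 remains conjecture. The match suggests an effect-size conversion error but does not prove one. The 0.46 equivalent also depends on the assumed pattern of a sustained effect; with two assessments it would be about 0.40. None of this makes the sentence true as a difference of d=0.20 from controls.

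A second objection is that power depends on a correlation the article does not state. That is right, and a reader might be tempted to quote one narrow band, such as 11-25%, as the actual power. That band holds only for r of about 0.5 to 0.8 and about 66 to 70 completers. At r=0.9 the planned test has 43%, and with all 100 children retained it has 62%. For the same reason it is too strong to say that the study can detect only moderate to large effects.

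A reader might also infer that a non-significant result will be taken as evidence against a small benefit. The article does not support this. It gives no rule for reading a null result, calls the study proof-of-concept, and plans replication in a larger cohort (although the small-sample limitation in the Discussion concerns generalisability, not power).

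**Conclusion.** The concern holds in this form: the published combination of 66 participants, d=0.20 and at least 80% power is not met for a between-group effect in this design at any usual correlation. At N=66 the planned test has about 11-43% power over r=0.5 to 0.9 (about 15-62% if all 100 are retained). The number needed for 80% over that range is 730 down to 148, or 788 for a single comparison.

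These figures rest on two-sided alpha 0.05, 1:1 allocation, equal correlations over time and an effect sustained at all later assessments. The conclusion does not depend on one choice of r: rescuing the claim with 66 children takes a correlation of about 0.95 for the planned test, or about 0.94 for an averaged follow-up contrast, and the article neither states nor supports either. The point must be fixed because a stated property of the design is wrong as written.

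**What to change.** Withdraw the claim of 80% power at d=0.20 and state instead the effect that 66 to 70 completers can detect. The new sentence should name the test, the effect-size metric (d or f, and how one was converted to the other), alpha and sidedness, and the authors' own justified within-child correlation. Possible wording, with the blanks for the authors to fill:

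> With 66 to 70 completers, 1:1 allocation and two-sided alpha of [ ], the group-by-time test has 80% power for a between-group difference of d=[ ] sustained at all three later assessments, assuming a within-child correlation of [ ], based on [source].

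If no correlation can be justified, give the range: d of about 0.65-0.67 at r=0.5, 0.50-0.52 at r=0.7, 0.41-0.42 at r=0.8 and 0.29-0.30 at r=0.9, for two-sided alpha 0.05.

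The cost is one rewritten sentence and a less favourable stated figure. It needs no extra children and no change to the training or assessments. Keeping d=0.20 as the target would instead require a larger sample: 294 to 730 completers for the planned test at r=0.8 to 0.5.
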